## Abstract

**Background:**

Intra-operative electrocorticography, based on interictal spikes and spike patterns, is performed to optimize delineation of the epileptogenic tissue during epilepsy surgery. High frequency oscillations (HFOs, 80–500 Hz) have been identified as more precise biomarkers for epileptogenic tissue. The aim of the trial is to determine prospectively if ioECoG-tailored surgery using HFOs, instead of interictal spikes, is feasible and will lead to an equal or better seizure outcome.

**Methods\Design:**

We present a single-blinded multi-center randomized controlled trial “The HFO Trial” including patients with refractory focal epilepsy of all ages who undergo surgery with intra-operative electrocorticography. Surgery is tailored by HFOs (arm 1) or interictal spikes (arm 2) in the intra-operative electrocorticography. Primary outcome is post-operative outcome after 1 year, dichotomized in seizure freedom (Engel 1A and 1B) versus seizure recurrence (Engel 1C-4). Secondary outcome measures are the volume of resected tissue, neurologic deficits, surgical duration and complications, cognition and quality of life. The trial has a non-inferiority design to test feasibility and at least equal performance in terms of surgical outcome. We aim to include 78 patients within 3 years including 1 year follow-up. Results are expected in 2018.

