Two decades after their first discovery there is a rising demand to know whether HFOs can be used in clinical practice and decision-making [14, 25, 26]. Tailoring based on HFOs in the ioECoG could improve the chance of seizure freedom. Other beneficial aspects could be a smaller resected area, with less chance of neurological deficits, which – together with an equal or increased seizure freedom rate – may lead to an overall better quality of life. Last but not least, the identification of epileptic HFOs can be automated [12, 27–30] and, therefore, could yield a future objective approach that is easily implemented.

“The HFO Trial” is a randomized controlled trial (RCT) designed to investigate the feasibility and safety of using HFOs during intra-operative tailoring of epilepsy surgery. The primary objective of this RCT is to validate if tailoring based on HFOs versus interictal spikes in the ioECoG during surgery will lead to the same post-surgical seizure outcome 1 year after surgery (non-inferiority design). Secondary objectives are comparison of the volume of resected tissue, the duration of the surgery, the occurrence of complications and neurologic deficits, and changes in cognitive functioning and quality of life. RCTs in the field of epilepsy surgery are not trivial undertakings [31, 32]. We report the details of our study design, and share our considerations for the trial set-up.

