## Methods

### Trial design

“The HFO Trial” is a single-blinded randomized controlled Dutch multi-center clinical trial. This trial is based on a non-inferiority design with an allocation ratio of 1:1. We chose a non-inferiority design, as we considered the primary objective of the study, to demonstrate that the intra-operative prospective use of HFOs to tailor surgery is feasible and will not lead to worse outcome than the widely applied method based on spikes. Secondary objectives of this study are to investigate whether the HFO-based, compared to spike-based, tailoring will lead to differences in the volume of resected tissue, neurologic deficits, surgical duration and complications, cognition and quality of life.

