### Sample size

The sample size calculation is based on a success rate of surgery (defined as Engel 1A or 1B at 1 year) in the control group (tailoring based on spikes) of 65 %, and the expected success in the experimental group (HFOs) of 80 %. The resulting margin is 15 %. Using a 1-sided 95 % confidence interval and a non-inferiority limit of 10 %, to acquire an 80 % power we need 39 patients per group. This results in a total of 78 patients. We anticipate that 80 % of the eligible patients will participate in the study.

We expect the potential loss-to-follow-up after the initial intervention to be low. Routine clinical visits to the neurosurgeon and neurologist are scheduled after surgery at 6 to 8 weeks, 6 months and 12 months. Our FU questionnaires coincide with these visits. Inclusions will proceed until the target sample size is achieved to address loss to follow-up. Loss to follow-up can be expected from; 1) withdrawal by the subject from the study during follow-up before the first preliminary outcome determination at 6–8 weeks, and 2) withdrawal from the study during the surgery by the surgeon or dedicated team due to urgent medical or technical issues.

Subjects are replaced if they withdraw from the study during follow-up before the first preliminary outcome determination at 6–8 weeks. Subjects who are withdrawn from the study during the surgery by the surgeon or dedicated team due to urgent medical or technical issues are also replaced.

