Tailoring based on spikes in the ioECoG is not an evidence-based method, as no RCT has compared tailoring to resection without ioECoG, but we relate to it as the “gold standard” [6]. The same restrictions for tailoring are valid for HFOs as for spikes. The ioECoG might either confirm the surgical plan or change the surgical plan, but reduction or extension of the planned resection might be limited by eloquent cortex or anatomy. Events, spikes or HFOs, occurring remote from the resection site are usually not considered indicative for removal. Upfront it may be hard to tell if tailoring will really influence the surgical plan, even though in our population we aim to perform ioECoG only with a valid indication. We will, prospectively, collect data on the influence of events on the actual clinical decision and perform a post-hoc analysis to clarify in which patients tailoring actually changed the surgical plan.

The visual analysis of HFOs requires experienced observers, and additional analysis time due to the offline analysis and expanded time settings for ECoG display. We estimate this additional analysis time is 5 to 10 minutes per ioECoG recording, compared to spike analysis. A disadvantage of using spikes is that they have a lower inter-observer agreement compared to HFOs [42]. An associated risk of the use of HFOs is undersampling and underdetection of HFOs compared to spikes, as HFOs are a more local phenomena than spikes [15], and the negative effect of anesthetics on the number of HFOs [24]. These concerns are preempted similar as for the procedures during tailoring based on spikes; multiple recordings are made before and after resection, where the sampling strategy is based on the results in previous recordings to guaranty optimal sampling. All recordings are made while tapering the propofol until a continuous EEG pattern can be seen.

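### The objective is worded as equal or not worse outcome, but the only criterion, a 10-point non-inferiority limit, can show only that HFO tailoring is less than 10 percentage points worse

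*Protocol article*

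**What the plan says.** The protocol article words its goal in four ways:

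- Abstract, Background: HFO tailoring "is feasible and will lead to an equal or better seizure outcome".
- Abstract, Methods\Design: "The trial has a non-inferiority design to test feasibility and at least equal performance in terms of surgical outcome".
- Background, primary objective: tailoring by HFOs versus spikes "will lead to the same post-surgical seizure outcome 1 year after surgery (non-inferiority design").
- Methods, Trial design: HFO tailoring "is feasible and will not lead to worse outcome than the widely applied method based on spikes".

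The criterion appears once. The Sample size section assumes 65 % success with spikes and 80 % with HFOs, calls the 15-point gain a margin, and in the next sentence sets a one-sided 95 % confidence interval and "a non-inferiority limit of 10" %, giving 39 patients per group for 80 % power.

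The Statistical methods section plans risk ratios and a risk difference with a 95 % confidence interval and a one-sided chi-square test. It does not mention the 10-point limit. The Considerations section says that a superiority design was not chosen because of the sample size it needs, and leaves proof of superiority to a larger trial. The Interim analysis section lets the monitoring committee advise stopping for superiority.

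**The concern.** A non-inferiority limit sets the strongest statement that a positive trial supports. Here that statement is that HFO tailoring loses less than 10 points of seizure freedom. None of the four wordings of the goal mentions the 10 points, and each promises more than the test can deliver. A reader of the final report could take a positive result as proof that no seizure freedom is given up, when a true loss of several points would not have been excluded.

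Two further features make this more likely. Calling the assumed 15-point gain a margin, just before the 10-point limit, blurs which figure is the threshold. And a one-sided chi-square test, which is ordinarily a test of zero difference, is not the test of a 10-point limit, so the analysis section does not say which comparison decides the trial.

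**Working it through.** **Inputs.** Control 65 %, HFO 80 %, limit 10 points, one-sided 95 % interval (z = 1.645), 80 % power (z = 0.842), 39 per group; all from the Sample size section. The method below is the unpooled normal approximation, which is my choice because the article names none.

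**1. The plan's own figure.**
n = [p_c(1-p_c) + p_t(1-p_t)] × (1.645 + 0.842)² / (p_t - p_c + 0.10)²
= [0.65×0.35 + 0.80×0.20] × 6.183 / 0.25²
= 0.3875 × 6.183 / 0.0625 = 38.3, rounded up to 39 per group. It reproduces.

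**2. What meeting the limit shows.** Lower bound = d - 1.645 × √{[p_t(1-p_t) + p_c(1-p_c)]/39}, where d is the observed difference. Suppose 25/39 controls (64.1 %) are seizure-free, close to the planned 65 %:

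| HFO successes | d (points) | SE (points) | lower bound (points) | above -10? | above 0? |
|---|---|---|---|---|---|
| 27/39 | +5.1 | 10.7 | -12.4 | no | no |
| 28/39 | +7.7 | 10.5 | -9.6 | yes | no |
| 31/39 | +15.4 | 10.0 | -1.1 | yes | no |
| 32/39 | +17.9 | 9.8 | +1.8 | yes | yes |

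From 28 to 31 HFO successes the limit is met while a true loss is still not excluded. The article's wording would describe such a result as at least equal.

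**3. How often the limit is met when HFO tailoring is truly worse.** P = Φ[(p_t - p_c + 0.10)/SE - 1.645], with control 65 %:

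- HFO 60 %: SE = √[(0.2275 + 0.2400)/39] = 0.1095; 0.05/0.1095 = 0.457; P = 11.7 % (12.0 % by exact enumeration).
- HFO 57 %: SE = √[(0.2275 + 0.2451)/39] = 0.1101; 0.02/0.1101 = 0.182; P = 7.2 %.
- HFO 55 %, on the limit: P = 5.0 %, as designed.

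**4. Power to read better from the same bound.** At 65 % against 80 %, SE = √(0.3875/39) = 0.0997; 0.15/0.0997 = 1.505; Φ(1.505 - 1.645) = 44.4 % (43.5 % with pooled variance). For 80 % power a one-sided superiority test would need 109 per arm, which agrees with the article's reason for not choosing that design.

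**5. Why the analysis section must name the bound.** If the 95 % interval in Statistical methods is read as two-sided (z = 1.960), 28/39 against 25/39 gives 7.7 - 1.960 × 10.5 = about -13 points and fails the limit, and power for non-inferiority falls from 80.6 % to 70.8 %. The same data can pass or fail, depending on a choice that this section leaves open.

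**The case against.** The strongest reply is that the abstract line itself says non-inferiority, the limit and the one-sided interval are explicit in the Sample size section, and at this size a positive trial would in practice have a favourable point estimate: against 25/39, HFO needs at least 28/39, an observed gain of 7.7 points. The probabilities of 11.7 % and 7.2 % are also what any non-inferiority test shows inside its margin. All of this is correct. It means that the overstatement concerns what has been excluded and not the direction of the estimate. It does not turn exclusion of a 10-point loss into equality.

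It can also be said that an ordered step from non-inferiority to superiority is commonly left to a statistical analysis plan, which is not shown. That stands, so the missing step is not an error in itself. It would not correct the published wording.

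A reader might infer three stronger criticisms that the article does not support:

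- **That the better half of the aim cannot be answered.** It can: the planned risk-difference interval can be read against 0, and the Considerations section says openly that proof of superiority is left to a larger trial.
- **That spike tailoring was never compared with surgery without ioECoG, so its effect is wholly unknown.** The article does say "Tailoring based on spikes in the ioECoG is not an evidence-based method", but the reason it gives is the absence of a randomized comparison. Its Background cites other studies on residual spikes and outcome, with conflicting results. Nor does the trial claim efficacy against surgery without ioECoG; its objective is relative to spike tailoring.
- **That only superiority would show that HFO tailoring works.** If spike tailoring were itself harmful, beating it would not show this either.

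**Conclusion.** The point holds as a mismatch between wording and criterion. A positive result would support less than 10 percentage points worse, and not at least equal, the same, or not worse. Against a 65 % control rate, true HFO rates down to just above 55 % lie within the limit. With 25/39 control successes, the results affected are 28 to 31 HFO successes out of 39. The mislabelled 15 points and the missing link between the final analysis and the limit are part of the same defect.

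The sample size has no arithmetic error, and making superiority a secondary hope is a reasoned choice. The figures rest on 39 evaluable patients per arm, a control rate near 65 % and the unpooled normal approximation; exact enumeration changes them by about one point or less. The point should be corrected, but it does not threaten the design.

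**What to change.** 1. In the abstract, the primary objective, the Trial design section and the planned conclusion, replace the equality wording by: seizure freedom with HFO tailoring is less than 10 percentage points worse than with spike-tailored surgery.
2. In Statistical methods, state that the lower one-sided 95 % bound of the risk difference (HFO minus spikes) is compared with -10 points for the primary conclusion. Only if that is met is the same bound compared with 0 for a claim of better. Add that power for this second step is about 44 % at the planned rates, in line with the statement that superiority is not the target. If the second step is not wanted, drop better from the aim.
3. In Sample size, call the 15 points the expected difference and keep the word margin or limit for the 10 points.

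The cost is a few sentences and a somewhat more modest claim. No patients are added. The fixed sequence uses no extra alpha at the final look. The interim efficacy analyses after 20 and 40 patients, with possible stopping for superiority, raise their own error-rate question, which this change does not settle.

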**Discussion:**

This trial provides a transition from observational research towards clinical interventions using HFOs. We address methodological difficulties in designing this trial. We expect that the use of HFOs as a biomarker for tailoring will increase the success rate of epilepsy surgery while reducing resection volume. This may reduce neurological deficits and yield a better quality of life. Future technical developments, such as validated automatic online HFO identification, could, together with the attained clinical knowledge, lead to a new objective tailoring approach in epilepsy surgery.

**Trial registration:**

This trial is registered at the US National Institutes of Health (ClinicalTrials.gov) #NCT02207673 (31 July 2014) and the Central Committee on Research Involving Human Subjects, The Netherlands #NL44257.041.13 (18 March 2014).

## Background

The current success rate of epilepsy surgery in patients with refractory focal epilepsy lies between 36 and 84 % after 1 year [1]. Intra-operative electrocorticography (ioECoG) can be performed during surgery to optimize delineation of the epileptogenic area by taking into account interictal spikes or spike patterns. This so called “tailoring” affects surgical decision-making [2]. Resection of areas with interictal spikes has been associated with seizure freedom [3–5], whereas remaining spikes after resection have been suggested to indicate poor surgical outcome [2, 3, 6], while other studies contradict this [7–9]. The value of tailoring by interictal spikes can be questioned as they represent the irritative zone rather than the seizure onset zone [6], spikes can spread into non-epileptic surrounding areas [6], and can also arise from surgical manipulation [10]. This leaves tailoring based on spikes in the ioECoG under international debate. Incomplete resection of so called “ictiform spike patterns”, consisting of recruiting patterns, repetitive bursting patterns or continuous rhythmic spiking, has been reported to predict poor outcome [11].

High frequency oscillations (HFOs, 80–500 Hz) are proposed as a new and more precise biomarker for epileptogenic tissue than spikes [12–20]. HFOs are an indicator of the seizure onset zone [15]. Removal of tissue with HFOs, especially fast ripples (FR, 250–500 Hz), is linked to good surgical outcome [16, 18, 21, 22]. The area showing HFOs usually overlaps with, but is smaller than the irritative zone showing spikes [15]. HFOs mirror epileptic disease activity as they are prominently found in focal cortical dysplasia (FCD), with increased numbers in the more epileptogenic FCD type 2 compared to type 1 [17], and they increase when anti-epileptic drugs are tapered [23]. HFOs can be recorded during surgery, after anesthetics are reduced [24].

Two decades after their first discovery there is a rising demand to know whether HFOs can be used in clinical practice and decision-making [14, 25, 26]. Tailoring based on HFOs in the ioECoG could improve the chance of seizure freedom. Other beneficial aspects could be a smaller resected area, with less chance of neurological deficits, which – together with an equal or increased seizure freedom rate – may lead to an overall better quality of life. Last but not least, the identification of epileptic HFOs can be automated [12, 27–30] and, therefore, could yield a future objective approach that is easily implemented.

“The HFO Trial” is a randomized controlled trial (RCT) designed to investigate the feasibility and safety of using HFOs during intra-operative tailoring of epilepsy surgery. The primary objective of this RCT is to validate if tailoring based on HFOs versus interictal spikes in the ioECoG during surgery will lead to the same post-surgical seizure outcome 1 year after surgery (non-inferiority design). Secondary objectives are comparison of the volume of resected tissue, the duration of the surgery, the occurrence of complications and neurologic deficits, and changes in cognitive functioning and quality of life. RCTs in the field of epilepsy surgery are not trivial undertakings [31, 32]. We report the details of our study design, and share our considerations for the trial set-up.

## Methods

### Trial design

“The HFO Trial” is a single-blinded randomized controlled Dutch multi-center clinical trial. This trial is based on a non-inferiority design with an allocation ratio of 1:1. We chose a non-inferiority design, as we considered the primary objective of the study, to demonstrate that the intra-operative prospective use of HFOs to tailor surgery is feasible and will not lead to worse outcome than the widely applied method based on spikes. Secondary objectives of this study are to investigate whether the HFO-based, compared to spike-based, tailoring will lead to differences in the volume of resected tissue, neurologic deficits, surgical duration and complications, cognition and quality of life.

### Participants

Participants are candidates for epilepsy surgery who are referred to the Dutch Collaborative Epilepsy Surgery Program (DCESP) and are selected to undergo epilepsy surgery with ioECoG-based tailoring. Members of the DCESP come from the two Dutch epilepsy centers and three Dutch university medical centers performing epilepsy surgery. The two participating surgical centers in this trial are: 1) the UMC Utrecht, specialized in pediatric epilepsy surgery with 75 % of the patients being < 18 years of age at surgery, and 2) the VUmc Amsterdam, that operates on adult patients only (≥18 years). Patients and parents or care givers will be asked to participate if they comply with the following eligibility criteria:Refractory focal epilepsy, defined as at least 2 seizures in the past 24 months, in spite the use of 2 or more different anti-epileptic drugs (AEDs).Epilepsy surgery planned with ioECoG to tailor the resection. Note that in the participating centers, this automatically excludes standard right-sided temporal resections, disconnections and hemispherectomies in which no ioECoG is performed.Command of the Dutch language by the patient or parents\legal representatives and capability of completing the Dutch questionnaires.Able to give informed consent.

Exclusion criteria are:Previous chronic ECoG (grid) monitoring preceding epilepsy surgery. This is a biased population, because results of the extensive pre-surgical work-up and the results of the monitoring period determine the outline of the resection. This includes precise knowledge of the seizure onset zone, the inter-ictal spikes and HFO areas.Patients with an occipital focus undergoing ioECoG. Physiological FRs have been described to occur in the occipital lobe [33]. We deemed it unsafe to perform HFO-guided resections in these patients, as it is still difficult to discriminate between pathological and physiological HFOs.

### Interventions

Participating patients who will undergo ioECoG-tailored surgery will be randomized into an HFO-guided (arm 1) or standard epileptiform spikes-guided (arm 2) resection.

The ioECoG is routinely recorded at a sampling frequency of 2048 Hz using clinical electroencephalogram (EEG) software. A dedicated HFO team, including two experienced HFO observers, will perform the analysis during surgery when the patient has been allocated to the HFO arm. The HFO reviewers need to achieve consensus about the HFOs and distinguish them from artifacts. This team will, together with the clinical neurophysiologist in charge, advise the neurosurgeon on the extent of the tissue to be resected. HFO analysis is performed visually and off-line using Stellate Harmonie Reviewer (v7.0, Montreal, QC, Canada), as this is currently the only clinical EEG software that provides HFO visualization and marking. A split screen modus will be used to simultaneously visualize ripples (settings: finite impulse response (FIR) filter > 80 Hz, gain 5 μV/mm) and fast ripples (settings: FIR filter > 250 Hz, gain 1 μV/mm) at an elongated time interval of 0.4 s/page, according to the settings described in other studies [15, 18, 21, 22]. Based on pilot data, we expect that the visual analysis of HFOs will require 50 % more time compared to the visual analysis of epileptogenic spikes, which usually takes 3 to 5 minutes per recording. This is an intention-to-treat study. HFOs in eloquent regions will not be resected, similar to standard tailoring practice based on spikes. In absence of HFOs, ictiform spike patterns (for definition see introduction) [11] will always be resected, irrespective of treatment allocation. If no HFOs or ictiform spikes are found a planned resection is performed according to size and location of epileptogenic structural lesion(s), similar to standard clinical practice when no spikes could be identified.

